|---------------------------------------------------------------------------------------------------------|----------------------|--------------------------------------------------------------------------------------------|
| [figure not shown]
MaaT Pharma | Appendix 1           | Protocol N°: MPOH02
EudraCT N° : 2015-004335-12
Version .1 9.0
Date : 28 Feb 2017 |
|                                                                                                         | Etude ODYSSEE |                                                                                            |

## Sample circuit

[figure not shown]

All documentation of **MaaT Pharma** is PROPRIETARY information and may not be forwarded to third parties without prior written consent from **MaaT Pharma**. Reproductions, either in part or in whole, may not be published or copied in any manner, without the explicit written consent of **MaaT Pharma**

|                                                                                                         |                      |                                                                                            |
|---------------------------------------------------------------------------------------------------------|----------------------|--------------------------------------------------------------------------------------------|
| [figure not shown]
MaaT Pharma | Appendix 1           | Protocol N°: MPOH02
EudraCT N° : 2015-004335-12
Version .1 9.0
Date : 28 Feb 2017 |
|                                                                                                         | Etude ODYSSEE |                                                                                            |

## REALISATION ET EVALUATION DE LA TRANSPLANTATION DE MICROBIOTE FECAL AUTOLOGUE

**A remplir par la personne ayant procédé à la transplantation**

Etiquette patient

N° identification patient:

### La veille de la transplantation

La transplantation s'effectue après arrêt des antibiotiques. Le jour de l'arrêt des antibiotiques, un prélèvement de selles doit être effectué en vue de l'analyse métagénomique et biochimique pour caractérisation de la dysbiose. Un lavement avec Normacol doit être effectué le soir de l'arrêt des antibiotiques.

Contacter MaaT Pharma (et/ ou le transporteur) au \_\_ . \_\_ . \_\_ . \_\_ . \_\_ pour convenir de l'envoi de l'inoculum pour le lendemain matin.

### Date et heure de dernière prise des antibiotiques:

le \_\_/\_\_/\_\_ à \_\_ h \_\_

Faire un lavement avec Normacol au patient.

A quelle heure le lavement a-t-il été effectué? à \_\_ h \_\_

Le lendemain, 2 heures avant la transplantation, faire un lavement avec Normacol au patient.

A quelle heure le lavement a-t-il été effectué? à \_\_ h \_\_

Attendre l'évacuation des selles.

Le patient a-t-il évacué les selles? Oui ☐ Non ☐

Procéder à la transplantation (page 2).

|                                                                                   |                      |                                                                                            |
|-----------------------------------------------------------------------------------|----------------------|--------------------------------------------------------------------------------------------|
| [figure not shown] | Appendix 1           | Protocol N°: MPOH02
EudraCT N° : 2015-004335-12
Version .1 9.0
Date : 28 Feb 2017 |
|                                                                                   | Etude ODYSSEE |                                                                                            |

Heure de fin de la transplantation : \_\_\_\_\_ h \_\_\_\_\_

Totalité de l'inoculum injectée : Oui ☐ Non ☐

Si non, préciser pourquoi :

-----

-----

-----

Le patient a-t-il évacué l'inoculum Oui ☐ Non ☐

Si oui, préciser l'heure : \_\_\_\_\_ h \_\_\_\_\_

Indiquer, si possible, le volume approximatif de perte \_\_\_\_\_ mL

|                                                                                   |                      |                                                                                            |
|-----------------------------------------------------------------------------------|----------------------|--------------------------------------------------------------------------------------------|
| [figure not shown] | Appendix 1           | Protocol N°: MPOH02
EudraCT N° : 2015-004335-12
Version .1 9.0
Date : 28 Feb 2017 |
|                                                                                   | Etude ODYSSEE |                                                                                            |

|                                                                        |
|------------------------------------------------------------------------|
| Evaluation de la faisabilité de la procédure de transplantation |
|------------------------------------------------------------------------|

A remplir par la personne ayant procédé à la transplantation

Entourer le chiffre correspondant

[figure not shown]

Très facile

Très difficile

**Commentaires (difficultés, problèmes rencontrés) :**

-----

-----

-----

**Signature opérateur :**

|                                                                                   |                      |                                                                                            |
|-----------------------------------------------------------------------------------|----------------------|--------------------------------------------------------------------------------------------|
| [figure not shown] | Appendix 1           | Protocol N°: MPOH02
EudraCT N° : 2015-004335-12
Version .1 9.0
Date : 28 Feb 2017 |
|                                                                                   | Etude ODYSSEE |                                                                                            |

## A REMPLIR PAR LE PATIENT

Entourer le chiffre correspondant

### Comment évaluez-vous la procédure de transplantation :

[figure not shown]

Très confortable

Très inconfortable

[figure not shown]

Pas de douleur

Très douloureux

### Comment vous êtes-vous senti immédiatement après la transplantation :

[figure not shown]

Très bien

Très mal

### Comment vous êtes-vous senti 4 heures après la transplantation :

[figure not shown]

Très bien

Très mal

|                                                                                                         |                      |                                                                                            |
|---------------------------------------------------------------------------------------------------------|----------------------|--------------------------------------------------------------------------------------------|
| [figure not shown]
MaaT Pharma | Appendix 1           | Protocol N°: MPOH02
EudraCT N° : 2015-004335-12
Version .1 9.0
Date : 28 Feb 2017 |
|                                                                                                         | Etude ODYSSEE |                                                                                            |

Si non, préciser pourquoi :

-----

-----

-----

Le patient a-t-il évacué l'inoculum

Oui ☐ Non ☐

Si oui, préciser l'heure :

\_\_\_\_ h \_\_\_\_

Indiquer, si possible, le volume approximatif de perte

\_\_\_\_ mL

### Evaluation de la faisabilité de la procédure de transplantation

A remplir par la personne ayant procédé à la transplantation

Entourer le chiffre correspondant

[figure not shown]

Très facile

Très difficile

**Commentaires (difficultés, problèmes rencontrés) :**

-----

-----

-----

**Signature opérateur**

**A REMPLIR PAR LE PATIENT**

Entourer le chiffre correspondant

All documentation of **MaaT Pharma** is PROPRIETARY information and may not be forwarded to third parties without prior written consent from **MaaT Pharma**. Reproductions, either in part or in whole, may not be published or copied in any manner, without the explicit written consent of **MaaT Pharma**

|                                                                                   |                      |                                                                                            |
|-----------------------------------------------------------------------------------|----------------------|--------------------------------------------------------------------------------------------|
| [figure not shown] | Appendix 1           | Protocol N°: MPOH02
EudraCT N° : 2015-004335-12
Version .1 9.0
Date : 28 Feb 2017 |
|                                                                                   | Etude ODYSSEE |                                                                                            |

**Comment évaluez-vous la procédure de transplantation :**

[figure not shown]

Très confortable

Très inconfortable

[figure not shown]

Pas de douleur

Très douloureux

**Comment vous êtes-vous senti immédiatement après la transplantation :**

[figure not shown]

Très bien

Très mal

**Comment vous êtes-vous senti 4 heures après la transplantation :**

[figure not shown]

Très bien

Très mal

**Comment vous êtes-vous senti le lendemain de la transplantation :**

All documentation of **MaaT Pharma** is PROPRIETARY information and may not be forwarded to third parties without prior written consent from **MaaT Pharma**. Reproductions, either in part or in whole, may not be published or copied in any manner, without the explicit written consent of **MaaT Pharma**

|                                                                                   |                      |                                                                                            |
|-----------------------------------------------------------------------------------|----------------------|--------------------------------------------------------------------------------------------|
| [figure not shown] | Appendix 1           | Protocol N°: MPOH02
EudraCT N° : 2015-004335-12
Version .1 9.0
Date : 28 Feb 2017 |
|                                                                                   | Etude ODYSSEE |                                                                                            |

[figure not shown]

**Commentaires :**

-----

-----

-----

|                                                                                   |                      |                                                                                          |
|-----------------------------------------------------------------------------------|----------------------|------------------------------------------------------------------------------------------|
| [figure not shown] | Appendix 2           | Protocol N°: MPOH02
EudraCT N°: 2015-004335-12
Version 1 9.0
Date : 28 Feb 2017 |
|                                                                                   | ODYSSEE study |                                                                                          |

## JOURNAL DE BORD PATIENT

A remplir par le médecin :

Nom Prénom : .....

Numéro d'inclusion: .....

Date d'inclusion du patient : \_\_\_\_/\_\_\_\_/\_\_\_\_

Etiquette Patient

### INSTRUCTIONS :

Remplir ce formulaire à chaque visite (V1, V2, V3, V4, V5), votre réponse doit se rapporter aux 24 heures précédentes. Ne pas se tromper de colonne. Reporter les évènements notables dans la partie « remarques ».

Dates des prélèvements de selles :

1er prélèvement : \_\_\_\_/\_\_\_\_/\_\_\_\_

2ème prélèvement : \_\_\_\_/\_\_\_\_/\_\_\_\_

3ème prélèvement : \_\_\_\_/\_\_\_\_/\_\_\_\_

Date de la 1ère transplantation fécale :

\_\_\_\_/\_\_\_\_/\_\_\_\_

Date de la 2ème transplantation fécale :

\_\_\_\_/\_\_\_\_/\_\_\_\_

[figure not shown]

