#### **4.6. Measurement of AFMT feasibility and acceptability**

The AFMT feasibility and acceptability will be evaluated by the physician and the patient on a visual analogic scale (**Appendix 1**). Before and after chemotherapy clinical tolerance will be monitored in a logbook evaluating every day mood and quality of life, digestive symptoms (appetite, nausea, bloating, discomfort, pain), transit and stool characteristics using Bristol stool scale. The logbook will be given to the patient during study admission and carefully completed until the end of the study (**Appendix 2**). A health questionnaire EQ-5D-5L will be given to the patient at 4 timepoints (D0, D29, D40, and D70 see below) to evaluate more precisely the impact of AFMT on the quality of life.

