### ***D30 and D31 (between D25 and D36 depending on patient's condition) - Fecal transplantation***

The AFMT will be performed 24 hours after antibiotics discontinuation and after aplasia completion. The patient will receive 2 inocula of 150 mL corresponding to a total of 60g (2 x 30g) of faeces, according to the procedure (**Appendix 1**). A rectal preparation for AFMT will include 2 enemas with "Normacol lavement" the night before and the morning of the procedure, enhancing the potential for FMT to provide a "fresh start" in repopulating the colonic habitat of the patient. Indeed, the lavage will enhance FMT success by flushing out residual faeces, antibiotics, and *C. difficile* bacteria, toxins and spores (83). The rectal preparation and AFMT will not be performed in case of persistent mucositis, colitis, or haemorrhoids, that constitute exclusion criteria. A third inoculum is available in case of technical incident (rejection of the inoculum by the patient within 1 hour after transplantation). Fecal transplantation is performed by a rectal probe introduced in the patient's rectum. A tubing, ending with a rectal probe, is directly connected to allow the inoculum to reach the colon. The patient will remain in lying position for 1 hour to ensure a good transplantation and avoid any loss. Patient's vital signs (blood pressure, pulse, temperature, respiratory rate) will be monitored during all the time of the transplantation process, until the expulsion of the remaining transplant but at least 2 hours after AFMT. Monitoring will also focus on the recovery of intestinal transit, onset of abdominal pain, occurrence of fever before the patient's hospital discharge. In case of severe adverse event, the hospitalization will be extended to treat the event. In case of procedure-related SAE or SADR (Serious Adverse Drug Reaction) during the first AFMT, the second AFMT will not be done. Post-transplant clinical tolerance will be monitored with a questionnaire (**Appendix 1**) and the logbook (**Appendix 2**).

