### ***D40 (between D35 and D 45 depending on patient's condition)- Visit 3 - Hospitalization for consolidation chemotherapy***

At this time, the patient will report to the physician any adverse reaction or severe event occurred since his hospital withdrawal using the logbook during admission visit. Particular attention will be given for occurrence of severe diarrhea, fever, abdominal pain, infectious events and concomittant medications. The patient will also receive a EQ-5D-5L questionnaire. Prior to the initiation of consolidation chemotherapy, faeces and blood will be collected for analysis (**Procedures will be provided by BIOFORTIS SAS** - biochemical and bacteriological

|                                                                                                         |                      |                                                                                               |
|---------------------------------------------------------------------------------------------------------|----------------------|-----------------------------------------------------------------------------------------------|
| [figure not shown]
MaaT Pharma | Protocol             | Protocol N°: MPOH02
EudraCT N° : 2015-004335-12
Version 10.0
Date : 20 November 2017 |
|                                                                                                         | ODYSSEE STUDY |                                                                                               |

analysis, control of the microbiota recovery by metagenomic and analysis of blood immune cells).

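### The visit-day logbook form in Appendix 2 cannot supply the daily or interval record the protocol body relies on, so about days 2 to 7 after the second transplantation have no structured patient data

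*Protocol*

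**What the plan says.** **The form.** Appendix 2 (Journal de bord patient) instructs: "Remplir ce formulaire à chaque visite (V1, V2, V3, V4, V5), votre réponse doit se rapporter aux 24 heures précédentes". The page the patient completes has five dated columns, V1 to V5. Its items are number of stools, Bristol consistency, blood in stool, abdominal pain, nausea, bloating, general well-being, appetite and fever above 38 °C. There are no day-by-day columns. A free-text field follows, with the instruction "Reporter les évènements notables dans la partie « remarques".

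**The protocol body.**
- Section 4.6: "clinical tolerance will be monitored in a logbook evaluating every day mood and quality of life, digestive symptoms", together with transit and stool characteristics. It adds: "The logbook will be given to the patient during study admission and carefully completed until the end of the study".
- Section 6.4.2, fecal transplantation: "Post-transplant clinical tolerance will be monitored with a questionnaire" (Appendix 1) and with the logbook (Appendix 2).
- Section 6.4.2, Visit 3: "the patient will report to the physician any adverse reaction or severe event occurred since his hospital withdrawal using the logbook during admission visit".
- Table 1: the row for Bristol stool evaluation by logbook is marked as required in all eight columns from D0 to D70. Three of these are intervals between visits: D0 to D30, D30 to D40 and D40 to D70.

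**The other patient instrument.** The patient part of Appendix 1 asks about comfort and pain of the procedure and about how the patient felt immediately, 4 hours after and on the day after transplantation. It goes no further than that day.

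**The concern.** The body treats the logbook as a running record, while the form takes one 24-hour snapshot per visit. Visit 2 comes before AFMT and Visit 3 about nine days after the second one, so the period in which tolerance of the procedure is of most interest lies between two snapshots.

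The study title calls this a feasibility and safety study, and short-term safety is a listed secondary objective. Section 4.4 names diarrhoea (severity and frequency), abdominal pain and bloating after AFMT as outcomes, and section 4.3 lists the number of stools per day as an input to the biosignature. A frequency over an interval cannot be obtained from a single 24-hour answer at its end. Section 9.1.2.2.1 exempts fever, abdominal pain, bloating and diarrhoea within 7 days of AFMT from immediate notification. A contemporaneous patient record would be especially useful for these symptoms, and daily entries that were never made cannot be recovered at analysis.

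**Working it through.** The plan gives no figure to reproduce. The check is a count of calendar days.

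**Inputs**
- First AFMT on day A1 and second on day A2 = A1 + 1. Nominal D30 and D31, window D25 to D36 (section 6.4.2).
- Visit 3 on day V. Nominal D40, window D35 to D45 (section 6.4.2).
- Last Appendix 1 item: day after the second AFMT, A2 + 1.
- Logbook recall at Visit 3: the previous 24 hours, counted generously as days V − 1 and V.

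**Formula.** Days covered by neither instrument run from A2 + 2 to V − 2. Their number is (V − 2) − (A2 + 2) + 1 = V − A2 − 3.

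**Nominal schedule.** 40 − 31 − 3 = 6 days, D33 to D38. These are days 2 to 7 after the second AFMT, or days 3 to 8 after the first. The gap takes up 6 of the first 7 days after the second AFMT (D32 to D38), and 5 of the first 7 after the first (D31 to D37).

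**Window combinations checked**

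| AFMT | Visit 3 | V − A2 − 3 | Days without structured entry |
|---|---|---|---|
| D30/D31 | D35 | 35 − 31 − 3 | 1 |
| D30/D31 | D40 | 40 − 31 − 3 | 6 |
| D30/D31 | D45 | 45 − 31 − 3 | 11 |
| D25/D26 | D35 | 35 − 26 − 3 | 6 |
| D25/D26 | D45 | 45 − 26 − 3 | 16 |
| D35/D36 | D40 | 40 − 36 − 3 | 1 |
| D35/D36 | D45 | 45 − 36 − 3 | 6 |

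**Logbook alone.** The readable Appendix 1 patient items cover comfort, pain of the procedure and general well-being. None concerns stool number, stool consistency, bloating or fever. For those items only the logbook counts. With Visit 2 on D29 and Visit 3 on D40 it leaves D30 to D38 empty, which is 9 days.

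**Other intervals.** The same mismatch holds for D0 to D30 and D40 to D70, which Table 1 also marks. The form has a V5 column (month 6), although Table 1 requires no logbook entry after D70. The form ends at V5, although section 4.6 runs the logbook to the end of the study, which is Visit 6 (month 12).

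**The case against.** The strongest reply is that events in this period are not lost. Table 1 requires adverse event monitoring in the D30 to D40 column. Section 9.1.2.3.1 has all adverse events, whatever their seriousness, entered in the CRF from first to last visit. Section 6.4.2 provides for monitoring of transit, abdominal pain and fever before discharge, and at Visit 3 asks about severe diarrhoea, fever, abdominal pain and infections. The form itself has a remarks field. The adverse event endpoint in section 7.2.3.1 counts subjects with at least one event and does not use logbook days.

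All of this stands. A reader might infer that days 2 to 9 after AFMT go unrecorded, or that adverse events will be under-counted. The documents do not support either. Only the structured entries are missing, and on the nominal schedule the gap ends at day 7 after the second AFMT. Under-reporting is a plausible risk with no figure behind it. No discharge date is fixed either, so the number of gap days spent at home is unknown.

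The wording of the body also leaves some room. The phrase in section 4.6 could be read as everyday mood rather than daily entries. An interval mark in Table 1 does not say daily, and Table 3 places stool number and consistency during hospitalization. These readings soften the word daily but do not reconcile the documents. On none of them does a form filled in at visits, asking about the last 24 hours, cover the D30 to D40 interval or give a patient a record of events since discharge. A remarks line is a useful prompt, but it yields no daily score or count.

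**Conclusion.** The point holds as an inconsistency between the protocol body and its own data collection form. Appendix 2 as built cannot deliver the record that sections 4.6 and 6.4.2 and the Table 1 stool row rely on. On the nominal schedule, 6 days (D33 to D38) have no structured patient symptom scores, stool counts or Bristol grades. The range is 1 to 16 days in the window combinations checked.

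Adverse event capture continues. After discharge it rests largely on recall at Visit 3, with a risk that mild fever, pain, bloating and diarrhoea are under-reported. The weakness affects secondary tolerance, acceptability and clinical-status data. It does not affect the two co-primary endpoints.

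This rests on two assumptions: that patients complete the form as instructed, and that the Appendix 2 at hand, marked version 9.0 while the body is version 10.0, is the form in use. It is the only form supplied.

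**What to change.** Give Appendix 2 dated daily columns, with the items unchanged, at least from the first AFMT to Visit 3. For the remaining periods (D0 to D30, D40 to D70, and V5 to the end of the study), reconcile section 4.6 and Table 1 with the form by stating where entries are daily and where they are visit-day only. Daily columns after AFMT alone would leave those periods contradictory. Visit-day entries could be kept there if the body text is changed to say so.

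The cost is a form amendment and one short entry per day from the first AFMT to the day before Visit 3. That is V − A1 = 40 − 30 = 10 entries per patient on the nominal schedule, and 5 to 20 over the window combinations above (35 − 30 = 5; 45 − 25 = 20). If section 4.6 means daily entries, the body already asks for them.
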